### Research questions

#### Primary research question

What is the effectiveness of the CSAM programmes in four states compared to the comparison/control state among children aged 6–59 months with uncomplicated SAM in rural India?

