### Sample size

The primary outcome of the study is cure rate at 12 weeks (in Chhattisgarh) or 16 weeks (in Telangana, Madhya Pradesh and Odisha) compared to the comparison area. Evidence on CMAM interventions in India testing its efficacy have shown cure rates ranging from 46.7 to 57.4% [19–23]. Another study from India found cure rate among 25–30% children with minimal community based interventions [26]. Hence for the sample size calculation, we therefore chose the expected cure rate with the proposed CSAM interventions of 50% and expected cure rate with existing government nutritional interventions of 25% to estimate the effect size of 25% (50–25%). The sample in each state will comprise of an equal proportion of children from the two age groups (6–23 months and 24–59 months). Using the significance level of 5%, with 80% power to detect the effect size of 25%, a design effect of 1.5 and accounting for 20% attrition due to loss of follow up and mortality, the sample size calculated for each age group of children is 100. Hence, the proposed sample size for the two age-groups of children in each state is 200 children. In total, the study will enroll 1000 children in all the five study states.

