### Data analysis

Final analysis will include all children enrolled in the study. Appropriate quantitative analyses will be used including descriptive statistics (proportion, percentage, mean or median), comparison of difference in proportion for binary outcome using Pearson chi-square and comparison of average change for continuous variable using t-tests. Recovery will be compared for effectiveness of state specific CSAM protocols and locally produced nutrient dense food supplements in four intervention states in comparison to the comparison state. Cox regression method will also be used for this analysis by defining recovery as event, as it can utilize the entire sample size including defaulters or loss to follow up. Other parameters including skinfold, defaulting, death, length of stay, average weekly weight gain and height gain will also be compared between the intervention states and the control state. Subgroup analysis will be done for comparing recovery among children aged 6–23 months and 24–59 months between intervention states and control state. For the sub-sample of body composition, change in fat mass, fat free mass and body water will be compared between the four intervention states and the comparison state. A linear mixed model will be developed for different outcomes (recovery, weight gain, and body composition parameters) adjusting for various random and fixed effects across all sites adjusted for differences at baseline.

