## Discussion

Different state governments have contextualized, designed and developed operational CSAM protocols for implementing their state specific CSAM strategies to be manageable within their existing NHM and ICDS systems. The study results will be generalisable to rural areas of India with a high burden of childhood wasting and underserved community. There are a large number of high-burden districts and Blocks in India where prevalence of SAM among children is very high. If the CSAM strategies of different states improve the study’s primary and/or secondary outcomes, the intervention strategies can be scaled up to all or parts of the high- burden districts through NHM and ICDS systems. These intervention strategies will also enable the health and ICDS systems to work in collaboration with each other at the village level through their existing frontline workers.

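### The Discussion lets improvement in any secondary outcome support scale-up, although cure rate is the single primary outcome and four states are each compared with one comparison state on many outcomes

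*Protocol article*

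**What the plan says.** - **Primary question.** The article asks: "What is the effectiveness of the CSAM programmes in four states compared to the comparison/control state". The Abstract and the Sample size section both name cure rate as the primary outcome. The Abstract lists weight gain, length of stay, body composition, relapse and mortality as secondary.
- **Sizing.** The Sample size section takes an "expected cure rate with the proposed CSAM interventions of 50" per cent and an "expected cure rate with existing government nutritional interventions of 25" per cent, and proceeds "Using the significance level of 5%, with 80% power to detect the effect size of 25" percentage points, with "a design effect of 1.5 and accounting for 20% attrition due to loss of follow up and mortality". This gives 100 children per age group and 200 per state.
- **Analysis.** Under Data analysis, recovery is compared "in four intervention states in comparison to the comparison state". Skinfold, defaulting, death, length of stay, weight gain and height gain are compared in the same way, as are fat mass, fat-free mass and body water in the sub-sample. Recovery is also compared within the two age groups, as a subgroup analysis.
- **Use of the results.** The Discussion says that if the state strategies improve the "primary and/or secondary outcomes, the intervention strategies can be scaled up to all or parts" of the high-burden districts.

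**The concern.** Naming one primary outcome limits what the study may claim. The Discussion removes that limit, because its wording allows scale-up to rest on a secondary outcome alone. With four states and about ten secondary comparisons in each, a false favourable result somewhere is much more probable than the nominal level of a single test suggests. The policy use is explicit: the Cost effectiveness analysis section also says its results are meant to inform scale-up. At stake is a recommendation to extend a programme that did not raise the cure rate.

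The shared comparison sample adds a second feature. A chance imbalance in it moves all four contrasts together, so false favourable results tend to come in groups.

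**Working it through.** **1. Reproduce the stated sample size.** Inputs from the Sample size section: 50% v 25%, 5%, 80% power, design effect 1.5, attrition 20%. Two-sided unpooled formula:

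n = (1.960 + 0.842)² × (0.50×0.50 + 0.25×0.75) / 0.25² = 7.849 × 0.4375 / 0.0625 = 54.9, rounded to 55.

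55 × 1.5 × 1.2 = 99, against the stated 100. The stated size therefore fits one pairwise test at an unsplit 5%. (Dividing by 0.8 for attrition gives 104.)

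**2. Error rates when no programme works.** Assumptions: two-sided 5% per test (the article gives 5% for sizing only), equal group sizes, correctly estimated variances, no confounding. Two contrasts that share an equal-sized comparison sample have correlation 0.5. Only results in the improving direction are counted, because the Discussion speaks of improvement.

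- *Cure, four states.* 1 − ∫ Φ(1.96√2 − x)⁴ φ(x) dx = 7.8%. With four independent comparison samples it would be 1 − 0.975⁴ = 9.6%.
- *Cure, both age groups, four states.* The age groups are different children, so 1 − (1 − 0.078)² = 15.0%.
- *Six outcomes, simulated with 400,000 replicates:*

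| Correlation between outcomes | Four states | One state |
|---|---|---|
| 0 | 38% | 14% |
| 0.3 | 32% | 12% |
| 0.5 | 28% | 10% |
| 0.8 | 19% | 7% |

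The one-state figure at correlation 0 can be checked by hand: 1 − 0.975⁶ = 14.1%. Across correlations 0 to 0.5, the single-state risk is four to six times the nominal 2.5%.

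*Sensitivity to the outcome count.* Eight outcomes (the Abstract's list, with body composition counted as three measures, plus cure) give 22–48% over four states for correlations 0.8 to 0. About twelve outcomes (adding those under Data analysis) give 25–62%.

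**3. Power if the four cure contrasts are adjusted.** 200 per state less 20% leaves 160, and 160 / 1.5 = 106.7 effective children per state. Pooled-variance formula, with mean proportion 0.375:

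power = Φ[(0.25√n − z√(2 × 0.375 × 0.625)) / √0.4375]

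| Level per contrast | z | Both ages pooled (n = 106.7) | One age group (n = 53.3) |
|---|---|---|---|
| 0.05 | 1.960 | (2.582 − 1.342)/0.661 → 97.0% | (1.826 − 1.342)/0.661 → 76.8% |
| 0.0146 (Dunnett) | 2.442 | (2.582 − 1.672)/0.661 → 91.6% | (1.826 − 1.672)/0.661 → 59.2% |
| 0.0125 (Bonferroni, first step of Holm) | 2.498 | (2.582 − 1.710)/0.661 → 90.6% | (1.826 − 1.710)/0.661 → 56.9% |

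**The case against.** - **The Discussion sentence is not a decision rule.** It sets no test, level or threshold, and process evaluation and cost-effectiveness would also inform the decision. This stands. A reader might infer that one significant secondary result formally triggers roll-out, and the text does not say so. It is still the only condition for scale-up that the article states, and it is looser than the choice of a single primary outcome implies.
- **Multiplicity methods belong in the analysis plan, which is not shown.** This stands for the method itself, so its absence is not the point made here. A method in the analysis plan would not change what the Discussion says the results justify.
- **Four distinct programmes are four questions.** Foods, screening and follow-up differ by state, and separate unadjusted conclusions on cure can be defended. This stands, so adjustment across states is conditional in the fix. It does not answer the single-state figure of 10–14%, which involves no adjustment across states.
- **The calculation is idealised.** The districts and blocks were chosen purposively, with one district per state, so state differences unrelated to the programme can shift a contrast. This stands. The figures exclude such bias, and Holm or Dunnett would not correct an atypical comparison district.

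**Conclusion.** The Discussion should be changed. As worded, it lets secondary outcomes carry a scale-up claim that the primary outcome does not support. At an assumed two-sided 5% per test and with no true effect, the chance of at least one false favourable result is about 8% on cure across four states, about 15% over both age groups, and about 28–38% over six outcomes. Within one state it is about 10–14%. The outcome count and the correlations of 0 to 0.5 are assumptions. Higher correlation lowers these figures and more outcomes raise them.

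Two stronger readings are tempting. One is that a false claim of benefit is likely, meaning more probable than not. Under the six-outcome assumption, figures above one half (53–64%) arise only if results in which a programme looks worse are counted too, and those could not support scale-up. In the favourable direction, one half is passed only with about twelve nearly uncorrelated outcomes, or if the tests also ignored clustering, which the article does not state. The other is that sharing one comparison state raises the chance of any false positive. It lowers it slightly (7.8% v 9.6%); its effect is to make errors occur together.

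**What to change.** In the Discussion, replace the scale-up condition with a statement that an effectiveness or scale-up claim for a state rests on the cure-rate contrast against the comparison state with both age groups pooled. Describe age-group and secondary results as supportive, reported as estimates with confidence intervals.

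If one overall claim is made across the four states, apply Holm or Dunnett to the four pooled-age cure contrasts. Pooled-age power falls from about 97% to about 91% and no extra children are needed.

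The cost is more than wording in one respect. The study was sized per age group, and under this change age-group results cannot carry the claim; their adjusted power would be only about 57–59%. The article should say so, and should state separately that adjustment across states does not protect against an atypical comparison district.

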**Methods:**

The longitudinal quasi-experimental study will be undertaken in two purposively selected blocks of one district each in the four intervention states and one comparison state. From each state, 200 SAM children identified using weight-for-length/height z-score (WHZ) < **−** 3 criteria will be enrolled in the study. Their anthropometric data and skinfold thickness will be taken on admission, at sixth week and at discharge by trained field investigators. Other child details, incidence of morbidity and socio-economic details will be collected on admission. To assess food consumption pattern including consumption of locally produced nutrient dense food supplements, dietary assessment, using 24-**h** dietary recall will be conducted on admission, at sixth week and at discharge. In addition, body composition parameters will be assessed for a sub-set of children using bio-electrical impedance analysis on admission and at discharge to analyse changes in total body water, fat-free mass, and fat mass. Post discharge, all study participants will be followed up monthly until 6 months. Atleast 10% of the sample will be checked for quality assessment.

The study’s primary outcome is cure rate defined as children attaining WHZ **≥** -2. Secondary outcomes include mean weight gain, mean length of stay, body composition parameters, relapse and mortality rates. Additionally, process evaluation and cost effectiveness analysis will be conducted.

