### Intervention strategy

In general, the State Governments of Telangana, Madhya Pradesh, Odisha and Chhattisgarh will implement community-based management of SAM (CSAM) programme adapted from the WHO guidelines, in addition to the existing government nutrition promotion interventions. The approach will incorporate active and/or passive case-finding and screening for severe wasting by government frontline nutrition and health workers. For uniformity, children with WHZ < -3 will be categorized as experiencing SAM. SAM children will further undergo medical examinations and appetite test to identify complicated and uncomplicated cases. All complicated cases will be referred to the nearest nutritional rehabilitation centres (NRCs) for in-patient management. All uncomplicated cases will be enrolled in the CSAM programme for their community-based management in *anganwadi centres*. While the program’s primary focus is on treatment of children who are severely wasted, key activities also include regular follow up of all enrolled children at the *anganwadi centers*, counseling of caregivers on infant and young child feeding (IYCF), safe water, sanitation and hygiene practices, family planning and child care practices, promotion of vaccinations, appropriate referrals of sick children to NRCs or public health facilities and post discharge follow up. SAM children enrolled in the programme will also be given locally produced nutrient dense food supplements, antibiotics, anthelminthic and micronutrient supplements. Key aspects of the state specific CSAM programme are presented in Table 1. Detailed description of the state specific CSAM protocols and nutritional content of each locally produced nutrient dense food supplement is provided in Additional file 1. In the comparison area, where no CSAM intervention is being implemented, SAM children identified and enrolled in the study will receive the existing government nutrition promotion interventions. The existing program includes provision of double quantity of Take Home Ration (THR)^1^ for severely underweight children (which covers most of SAM children) and identification and referral of SAM children to Malnutrition Treatment Centres (MTCs).

**Table 1 Tab1:** Key aspects of the CSAM protocol that vary per state assessed

States	Screening & Identification	Admission criteria	Maximum treatment duration	Discharge criteria	Nutrient dense food	Post-discharge Follow up

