### Data collection, cleaning and storage

In the intervention states, the children enrolled in the study will be managed according to the state specific CSAM guidelines and locally produced nutrient dense food supplements. The study will assess the effectiveness of the CSAM programmes in terms of recovery of these children compared to the comparison arm. This will be assessed using anthropometric (length/height and weight) measurements and skinfold thickness (triceps and sub-scapular) to be taken on admission, at sixth week and at discharge by the trained field investigator. For anthropometric measurements, a digital weighing machine with a sensitivity of 10 g to measure weight and a wooden infant-cum-stadiometer to measure length/ height will be used. Length and height will be measured to the nearest 0.1 cm, weight to the nearest 0.01 kg and skinfold thickness to the nearest 0.1 cm. Weighing equipment will be calibrated using standard calibration weights and infant-cum-stadiometer will be calibrated with calibration rods. The skinfold caliper will also be calibrated daily. Before doing the data collection work, all Field Investigators will be trained and also complete anthropometric standardization exercises where their anthropometric measurement skills will be assessed for thoroughness, accuracy and precision. To assess the accuracy and precision of each Field Investigator, their measures will be compared to those of the master trainers, who will be considered the gold standard. Intra-observer technical error of measurement (TEM) and reliability will be calculated using the difference between the two measures of the Field Investigators. Inter-observer TEM and reliability will be calculated by comparing the Field Investigators two measures to the trainer’s measure [27].

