Also, during admission and at discharge, the Field Investigator will administer the questionnaire for capturing child details and incidences of morbidity. Additionally, during admission, data on availability of drinking and sanitation facilities and other household level socio-economic information will be collected. Also,24-h dietary recall, food frequency and food consumption questionnaires will be administered to these children on admission, at sixth week and at discharge to study food consumed by the children, food frequency and compliance of locally produced nutrient dense food supplements provided to the children as part of the intervention. Futhermore, we will also ascertain cause of death of any enrolled child died during the study period.

Besides, first 100 enrolled children in that state who qualifies for body composition measurement i.e. weight on admission > 5 kg, will also be measured for body composition parameters using BIA machine (InBody S10) on admission and at discharge.

Post discharge, the children will be followed up on a monthly basis for anthropometry until 6 months by the field investigators. Additionally, skinfold thickness and body composition assessment of all children will also be repeated at sixth month post discharge. A detailed description of data collection process is shown in Table 2.

**Table 2 Tab2:** Overview of all measurements that will be taken from children

Parameters	Method	Admission/ Baseline	6th Week	12th/16thweek/Exit/Discharge	Post-discharge Follow up^b^
All children enrolled:					
Child details, and history of illness	Questionnaire	**✓**		**✓**	
Drinking water and sanitation facilities and other household socio-economic status		**✓**			
Weight, Recumbent length/ Height,	Digital weighing machine, Infantometer/ Stadiometer	**✓**	**✓**	**✓**	✓
Skinfold Thickness (triceps & subscapular skinfold)	Holtain Skinfold Caliper	**✓**	**✓**	**✓**	✓^c^
Dietary assessment (24-h dietary recall & food frequency) and Consumption of locally produced nutrient dense food	Observation and questionnaire	**✓**^**a**^	**✓**	**✓**	
Body composition; For enrolled sub-sample of children (weight > 5 kg)					
Body fat mass	BIA machine	✓		✓	
Body lean mass					✓^c^

^a^At baseline only the 24-h dietary recall & food frequency assessment will be done

^b^Post discharge, all children will be prospectively followed up for anthropometric measurements on a monthly basis till 6 months by the field investigators

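### The planned Cox model for recovery appears to combine near-exact event times in CSAM states with coarse visit-dated times in the comparison state, and the comparison state's final week is not fixed; both tilt the hazard ratio towards CSAM.

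*Protocol article*

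**What the plan says.** - **Model.** The Data analysis section lists Pearson chi-square for binary outcomes and then adds: "Cox regression method will also be used for this analysis by defining recovery as event". The reason given is that Cox regression can use all children, including defaulters and those lost. Interval censoring and a common visit grid are not mentioned.
- **Event.** In the Abstract the "primary outcome is cure rate defined as children attaining WHZ" of −2 or above. Table 1 gives the same threshold as the discharge criterion in all four CSAM states.
- **Readings.** Under Data collection, anthropometry is "to be taken on admission, at sixth week and at discharge by the trained field investigator". Table 2 has one schedule for all enrolled children: baseline, week 6 and a column headed "12th/16thweek/Exit/Discharge", followed by post-discharge follow-up.
- **Programme contact.** Under Intervention strategy, the "key activities also include regular follow up of all enrolled children at the" anganwadi centres. No frequency is given.
- **Comparison state.** The same section reads "In the comparison area, where no CSAM intervention is being implemented", and children there receive existing government services. No WHZ-based exit is described, although the Data analysis section says: "Other parameters including skinfold, defaulting, death, length of stay, average weekly weight gain and height gain will also be compared" with the control state.
- **Horizon.** The Sample size section sets the primary outcome as "cure rate at 12 weeks (in Chhattisgarh) or 16 weeks (in Telangana, Madhya Pradesh and Odisha) compared to the comparison area". It does not say at which of these weeks the comparison state is read. Table 1 instead gives 12 weeks to Madhya Pradesh and 16 weeks to Chhattisgarh.

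**The concern.** A Cox model compares the order in which events occur, so the groups must have their events dated in the same way. A CSAM child who reaches the threshold in week 7 is discharged and measured at about that time. A comparison child with the same growth, if seen only at the scheduled visits, is not recorded as recovered until week 12 or 16. One group's times are close to exact and the other's are interval-censored over 6 to 10 weeks, yet an ordinary Cox fit takes both at face value. CSAM then appears faster even when it is not.

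A second problem concerns the horizon. If a 12-week state is compared with children last read at week 16, the CSAM children have left the risk set before any comparison recovery after week 6 is counted.

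At stake is the hazard ratio for recovery, a stated analysis of the primary outcome in a study meant to inform scale-up.

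**Working it through.** **Inputs from the Sample size section.** Cure 25% (existing services) and 50% (CSAM), 5% significance, 80% power, design effect 1.5, 20% attrition, 200 children per state. The plan's own figure reproduces, taking the test as two-sided with unpooled variance: n = (1.96 + 0.84)² × (0.50×0.50 + 0.25×0.75) / 0.25² ≈ 54.9, rounded up to 55; 55 × 1.5 × 1.2 = 99, against the stated 100 per age group. After 20% attrition, 200 × 0.8 = 160 children per state are analysed.

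**Assumptions, not in the article.** Identical exponential recovery in both states; CSAM recovery detected every 1, 2 or 4 weeks; comparison recovery detected only at week 6 and the final visit; no clustering.

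**Step 1: how the comparison recoveries are dated.** With proportion p recovered by week 16, the proportion recovered by week w is 1 − (1 − p)^(w/16).

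| p by week 16 | By week 6 | By week 12 | Recovered in weeks 6–16, all dated week 16 |
|---|---|---|---|
| 25% | 10.2% | 19.4% | 25 − 10.2 = 14.8% |
| 50% | 22.9% | 40.5% | 50 − 22.9 = 27.1% |

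More than half of comparison recoveries carry the final-visit date, while the CSAM equivalents are spread over the interval.

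**Step 2: equal horizons.** Simulated Cox fits, Efron ties, 160 per state, no true difference:

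| Recovery | Hazard ratio, CSAM vs comparison | Two-sided 5% test rejects |
|---|---|---|
| 25% | about 1.03–1.07 | 4–7% |
| 50% | about 1.04–1.18 | 6–19% |

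Separate runs with 200 per state and a 16-week horizon agree in direction. At 50% recovery, detection on the exact day, weekly, 2-weekly and 4-weekly gave hazard ratios of 1.20, 1.18, 1.13 and 1.11, with rejection of 24%, 22%, 16% and 11%. At 25% recovery they gave 1.05–1.08 and 6–7%. Breslow ties at 50% gave 1.15–1.29 and 13–42%, so tie handling matters as well. The simulated cure proportions were equal in the two states throughout.

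**Step 3: a 12-week state against a comparison last read at week 16.** Let λ be the common recovery rate. While the 12-week children are at risk, their recorded cumulative hazard is 12λ. The comparison records only 6λ over the same period, because everything after week 6 is dated week 16. The ratio is 12λ / 6λ = 2, whatever the recovery rate. Simulation agrees: hazard ratio about 1.9–2.05, rejection 56–94%. In one set of runs, weekly, 2-weekly and 4-weekly detection gave 1.98, 1.97 and 2.03 at 25% recovery, and 1.97, 2.01 and 1.88 at 50%. Detection frequency hardly matters, so the unequal horizon is the cause.

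**Step 4: does a common grid remove it?** With both states placed on the same week-6 and week-16 grid, the hazard ratio was 0.99–1.00 and rejection about 4%. A complementary log-log model on the grouped intervals gave hazard ratios of 0.999 and 1.002, with rejection of 4.8% and 4.0%.

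**The case against.** - **The visit pattern in the comparison state is inferred.** Table 2 gives one schedule for all children, and the planned comparison of length of stay presupposes some exit date in the control state too. The full protocol may define it. This stands: the article does not support a flat claim that comparison children are seen only at week 6 and at the end. CSAM weighing frequency is also not given.
- **The hazard ratio near 2 is not a dating effect.** A reader might take it as the size of the coarse-versus-exact problem. It is not; it needs unequal horizons. Table 2 is as consistent with a week-12 comparison reading as with week 16, and with equal horizons the bias is far smaller.
- **Under no effect, recovery should be near the planned 25%.** A reader might infer that false positives rise well above 5%. With equal horizons they do not at that rate; this requires recovery nearer 50% without CSAM, plus frequent CSAM contact.
- **Cox is an additional analysis.** The sample size rests on cure proportions. A reader might infer that the chi-square comparison is biased as well, but timing alone does not affect it.
- **Dating rules often belong in an analysis plan.** That is fair for tie handling. But the article names a model that does not fit the reading schedule as it appears, and leaves the comparison state's horizon open while giving CSAM states different ones.

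**Conclusion.** The point holds in conditional form. If comparison children are read only at week 6 and a final visit, as Table 2 suggests, the ordinary Cox hazard ratio is tilted towards CSAM under identical recovery. With equal horizons the tilt is negligible to small at the planned control rate of 25% and moderate at 50%. It becomes severe only if a 12-week state is set against a comparison last read at week 16, a possibility that the article leaves open. The sizes rest on exponential recovery, the assumed detection frequencies and independence between children. Direction was the same in every scenario run. This is worth correcting before analysis; it does not undermine the primary comparison of cure proportions.

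**What to change.** In the Data analysis section, replace ordinary Cox regression with a grouped-time proportional-hazards model: a binary model with complementary log-log link on the intervals 0 to week 6 and week 6 to a final week common to both states, each CSAM recovery being placed in the interval where it occurred. An interval-censored proportional-hazards model is an equivalent choice. Either still gives a hazard ratio and still uses children with incomplete follow-up.

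State the week of the comparison state's final treatment-phase reading and how exit is defined there. Reconcile Table 1 with the Sample size section on which state has 12 weeks. Where final weeks differ and no comparison reading exists at the shorter horizon, use the interval-censored likelihood or restrict that contrast to the week-6 interval. Add no visit.

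**Cost.** Wording and analysis code only. Some timing detail in the CSAM states is lost, and a child lost part-way through an interval contributes less than under Cox; restricting a contrast to week 6 discards later recoveries. The change corrects dating only: it does not deal with children whose WHZ crosses the threshold and falls back between readings.
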